## Abstract

**Background:** Disinvestment from inefficient or ineffective health services is a growing priority for health care systems. Provision of allied health services over the weekend is now commonplace despite a relative paucity of evidence supporting their provision. The relatively high cost of providing this service combined with the paucity of evidence supporting its provision makes this a potential candidate for disinvestment so that resources consumed can be used in other areas.

This study aims to determine the effectiveness, cost-effectiveness and safety of the current model of weekend allied health service and a new stakeholder-driven model of weekend allied health service delivery on acute medical and surgical wards compared to having no weekend allied health service.

**Methods/Design:** Two stepped wedge, cluster randomised trials of weekend allied health services will be conducted in six acute medical/surgical wards across two public metropolitan hospitals in Melbourne (Australia). Wards have been chosen to participate by management teams at each hospital. The allied health services to be investigated will include physiotherapy, occupational therapy, speech therapy, dietetics, social work and allied health assistants. At baseline, all wards will be receiving weekend allied health services. Study 1 intervention will be the sequential disinvestment (roll-in) of the current weekend allied health service model from each participating ward in monthly intervals and study 2 will be the roll-out of a new stakeholder-driven model of weekend allied health service delivery. The order in which weekend allied health services will be rolled in and out amongst participating wards will be determined randomly. This trial will be conducted in each of the two participating hospitals at a different time interval. Primary outcomes will be length of stay, rate of unplanned hospital readmission within 28 days and rate of adverse events. Secondary outcomes will be number of complaints and compliments, staff absenteeism, and patient discharge destination, satisfaction, and functional independence at discharge.

(Continued on next page)

\* Correspondence: [contact]

Allied Health Research Unit, Monash Health and Physiotherapy Department, Monash University, Melbourne, Victoria, Australia

Full list of author information is available at the end of the article

(Continued from previous page)

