## Methods/Design

### Design

This research comprises two studies. Study 1 will consist of two hospital sites undertaking a novel, stepped wedge, roll-in, cluster randomised disinvestment trial whereby the current model of weekend allied health service delivery will be 'rolled back in' (withdrawn). Study 2 will consist of these same two hospital sites undertaking a conventional stepped wedge, roll-out, cluster randomised trial design in which a new stakeholder-driven model of weekend allied health service delivery will be rolled out to the same wards. Study 2 will commence immediately following completion of study 1.

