**Table 1 Caseload in participating wards**

| Hospital           | Ward             | Description                                                         |
|--------------------|------------------|---------------------------------------------------------------------|
| Dandenong Hospital | SW3/W2 acute     | Orthopaedic surgery                                                 |
|                    | SW4              | Stroke unit                                                         |
|                    | West 3           | Thoracic, Vascular, General surgical and medical units              |
|                    | West 4           | General medicine                                                    |
|                    | North Ward       | Head and neck, Plastics                                             |
|                    | North 3          | Surgical                                                            |
| Western Hospital   | 2B               | Medical                                                             |
|                    | 2C               | Medical                                                             |
|                    | 2D               | Infectious diseases; Respiratory medicine                           |
|                    | 2 W a | Plastics; Head and neck surgery; ENT surgery                        |
|                    | 3 W              | General surgery; Colorectal; Breast; Endocrine; Urology             |
|                    | 3E               | General surgery; Vascular surgery; Thoracic; Upper gastrointestinal |

aStudy 1 only.

different time points (Dandenong Hospital commencing February 2014 and Western Hospital (Footscray) commencing April 2014).

Data in this study will be collected from three groups of participants. Each group of participants is now described in detail.

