#### **Group 1**

'All patients on participating wards.' This group will consist of patients admitted to acute medical or surgical wards involved in the trial who are over the age of 18 years. Paediatric patients will be excluded from this study as they are not routinely seen on the selected wards (none are paediatric units or have paediatric beds) and have different provisions for service delivery. It is anticipated, based on previous patient flow data, that each ward will have an average of 174 patient admissions per month during the trial. This means that 6 wards at 1 site will have 7,308 patient admissions during the 7 months of study 1 and 7,308 during the 7 months of study 2. This will lead to an anticipated total of 29,232 patient admissions during the overall study period.

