#### **Study 1 intervention condition - current weekend allied health services**

Current physiotherapy, occupational therapy, social work, dietetics, speech pathology and allied health assistant weekend service delivery on the participating wards will be the intervention for study 1 of this trial. During this study, the weekend allied health services of each participating ward (cluster) will be 'rolled in' sequentially using the stepped wedge design (Figure 1 and Additional file 1). The current model of weekend allied health service delivery in the hospitals participating in this study has not been developed systematically, rather in an '*ad hoc*' manner driven by decisions made by individual allied health managers. Thus, there is potential that this model is not currently tailored to the needs of individual wards and is, therefore, not delivering optimal outcomes. However, it is the prevailing model of care that in a pragmatic research design serves as an appropriate reference standard [23].

Design at Western Hospital (Footscray) is similar but with 5 wards involved in study 2 and a 13-month total study period. Black = current weekend allied health service. White = no weekend allied health service. Grey = new, stakeholder-driven weekend allied health service. Twelve months of pre-trial data collection at participating sites indicated that weekend allied health services at each site varied in terms of the number of disciplines involved, the amount of time allocated per ward and the total budgetary allocation to this activity. Steps will be taken during study 1 to ensure intervention fidelity relative to the pre-trial data collection. Allied health staff providing weekend services will be updated as to the amount of time spent on each ward per month and will have pre-trial data used as monthly targets to ensure that service provision levels within study 1 intervention periods are consistent with pre-trial data. Staff will be advised to continue performing tasks and prioritising patients in the same manner with which they had been doing so prior to trial commencement.

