### **Study 2 - control condition - no weekend allied health services**

This will be identical to the study 1 control condition.

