patients who are exposed to both control and intervention conditions within each study will be excluded from the analyses. Analyses will be adjusted for index study ward (first study ward the patient was admitted to during that inpatient episode of care), calendar time using each step in the wedge design as a categorical covariate and for historical data collected for the outcome being examined from each site over the previous 2 years mapped against these steps to account for potential local seasonal variations in the outcomes collected.

Analyses will be conducted at a site-level with pre-planned meta-analyses across both sites using patient-level data from phase 1 and separately for phase 2. These meta-analyses will examine the main effect of the usual care weekend allied health service as opposed to the control condition across sites. A site-by-intervention interaction effect will also be examined to determine if there is heterogeneity in results between sites. This is plausible as a dose-response relationship may exist between the amount of resource allocated to the weekend allied health service and the study outcomes. In this study, local data collected prior to the study indicated that Dandenong Hospital allocated approximately four times as much resource to the acute medical and surgical wards participating in this research. Meta-regression will be employed using ward-level data, treating each ward over time as a pre-post intervention study to identify if the labour costs consumed on each ward for provision of the weekend allied health service explains variation in the change in each outcome within ward.

Patients who are exposed to both intervention and control conditions will be excluded from analyses to minimise potential contamination that is made possible by having the transition periods within the stepped wedge design.

**Study 2** These analyses will be equivalent to the analyses conducted for study 1; however, non-inferiority analyses will not be conducted for this study.

A grand meta-analysis is planned, pooling results between studies 1 and 2 to examine whether there is a significant study-by-intervention interaction effect. This analysis will examine whether the effect of the stakeholder-driven model of weekend allied health service was significantly different to that of the usual care weekend allied health service delivery model.

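### The grand meta-analysis reads the study-by-intervention interaction as a difference between the two service models, but that contrast is not randomised and is aligned with study period and time since withdrawal

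*Protocol*

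**What the plan says.** The Study 2 paragraph of the Protocol's Statistical analysis section plans a grand meta-analysis, "pooling results between studies 1 and 2 to examine whether there is a significant study-by-intervention interaction effect", and states what that interaction is to tell the reader: "This analysis will examine whether the effect of the stakeholder-driven model of weekend allied health service was significantly different" from that of usual care.

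Other sections fix the conditions under which the two effects are estimated:

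- **Order** (Design): "Study 2 will commence immediately following completion of study 1". Study 1 takes the service away from wards one at a time; study 2 gives a new service back to the same wards one at a time.
- **Control condition** (study 2 control section): "This will be identical to the study 1 control condition". Nothing is said about how long a ward has been without the service.
- **Wards** (Table 1 footnote): Western ward 2W takes part in study 1 only. The section on deviations from the registered protocol adds that case-mix at Western will probably change during study 2.
- **Adjustment** (Statistical analysis): index ward, step as a categorical covariate, and two years of site-specific historical outcome data mapped to the steps. Patients exposed to both conditions within a study are excluded.

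The section attaches no caveat to the comparison of the two models.

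**The concern.** Randomisation sets the order of wards within each study. It supports the comparison of service with no service in study 1, and again in study 2. It does not support a comparison of one service model with the other, because model coincides completely with study period and with direction of change.

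The interaction isolates the model only if the effect of having no service is the same quantity in both studies. The wedge makes that doubtful. Study 1 control wards have recently lost the service; study 2 control wards are the same wards, usually some months later. If outcomes react temporarily to withdrawal, or if harm from withdrawal builds up slowly, study 1 and study 2 estimate different things even when the two models are equally good.

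This is the only planned analysis that compares the two models directly. A significant interaction could be reported as showing that one model is better, when the design cannot tell that apart from study period or ward history.

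**Working it through.** **Inputs.** Steps are monthly (Abstract: "from each participating ward in monthly intervals"). Durations are in Group 1: "7,308 patient admissions during the 7 months of study 1 and 7,308 during the 7 months of study 2". This matches six wards and seven steps: 174 × 6 × 7 = 7,308. For Western: "Design at Western Hospital (Footscray) is similar but with 5 wards involved in study 2 and a 13-month total study period", that is 7 + 6 months. Start dates: "Dandenong Hospital commencing February 2014 and Western Hospital (Footscray) commencing April 2014". The plan gives no figure for the interaction, so there is none to reproduce.

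**1. Calendar.** With consecutive months, Dandenong runs February–August 2014 and then September 2014–March 2015. Western runs April–October 2014 and then November 2014–April 2015. The two studies share only the calendar months February–March at Dandenong and April at Western.

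**2. Time since withdrawal, six-ward site.** In study 1 the wards contribute m = 6, 5, 4, 3, 2, 1 control months, 21 in total.
- First month after withdrawal: 6 of 21 (29%).
- First two months: 5 × 2 + 1 = 11 of 21 (52%).
- Mean month: Σ m(m+1)/2 ÷ 21 = 56/21 = 2.7, range 1–6.

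In study 2 a ward that ended study 1 with m months off and has c further control months contributes months m+1 to m+c. The sum over wards is Σmc + 56.
- Averaged over all 720 orders, Σmc = 21 × 21/6 = 73.5, so the mean is (73.5 + 56)/21 = 6.2. By order it runs from (56 + 56)/21 = 5.3 to (91 + 56)/21 = 7.0. Individual months range from 2 to 12.
- First two months: only the first study 2 month of the last ward withdrawn, 1 of 21 (5%).

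For Western's five-ward study 2 the mean is 5.8 months (range 2–11).

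**3. What the ward + step model does with this.** The estimate is Σ x̃y / Σx̃², where x̃ is the no-service indicator after removing ward and step means; Σx̃² = 3.333 for six wards. Suppose neither model has a lasting effect and withdrawal shifts the outcome by d for a short time.
- One month, study 1: 2.5/3.333 = 0.75d.
- Two months, study 1: 3.810/3.333 = 1.14d.
- Two months, study 2: one affected cell, x̃ between −0.357 and +0.357, giving −0.107d to +0.107d and 0 on average.

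A spurious interaction of about 1.1d follows, in favour of the current model.

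**4. A different mechanism.** Let both models have the same full effect, 0.02, with changes that build up in equal monthly steps. Pool the sites (6 and 6 wards, then 6 and 5) with 7,000/42 = 166.7 patients per cell. At an event rate of 0.11, the interaction SE = √[(0.11 × 0.89/166.7) × (1/6.667 + 1/5.667)] = 0.0138.

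| Months to full effect: withdrawal / restoration | Study 1 | Study 2 | Interaction | Rejection at 5% |
|---|---|---|---|---|
| 1 / 1 | 0.0200 | 0.0200 | 0 | 5% |
| 2 / 1 | 0.0125 | 0.0200 | 0.0075 | 8% |
| 3 / 1 | 0.0074 | 0.0200 | 0.0126 | 15% |
| 6 / 1 | 0.0017 | 0.0188 | 0.0172 | 24% |
| 1 / 3 | 0.0200 | 0.0069 | −0.0131 | 16% |
| 3 / 3 | 0.0074 | 0.0070 | −0.0004 | 5% |

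At a rate of 0.41 (SE 0.0218) the asymmetric cases give 6–13%. The sign depends on which change is slower; if both are equally slow, the bias nearly vanishes. The durations are assumptions.

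**5. Ward set.** A six-ward wedge carries information 3.333 and a five-ward wedge 2.333. Dandenong's pooled weight moves from 0.50 to 3.333/5.667 = 0.59. With site effects of 0.02 and 0, the pooled effect shifts by 0.02 × 0.088 = 0.0018.

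**The case against.** The strongest reply has four parts.

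- **Adjustment.** The plan does adjust for ward, step and historical seasonal outcomes, so a reader who infers that season is ignored would be wrong. This stands. These terms remove differences in outcome level; what remains is a service effect that itself varies by season, case-mix or time since the change. Excluding patients exposed to both conditions removes some transition caseload, but not patients newly admitted in the months after a change.
- **Size.** A reader might infer from 1.1d that the interaction will be biased by a known amount towards the current model. The documents do not support that. They give no value for d, no duration and no evidence of a disturbance, and other equally possible patterns reverse the sign or cancel. Nor is study 1 control time mostly the first weeks: 6 of 21 ward-months are the first month, and the ranges of time since withdrawal overlap.
- **Wards.** The loss of 2W is disclosed and matters little by itself (0.0018 in the example). The case-mix change that the protocol expects at Western is the stronger point.
- **Scope.** This is one supplementary analysis, and the sentence poses a question without claiming randomised evidence. Detailed model terms can be left to an analysis plan. That is fair for the extra terms. It does not cover the interpretation, which the protocol itself states.

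**Conclusion.** The point holds as one of interpretation. The study-by-intervention interaction is an indirect, non-randomised contrast, fully aligned with study period, direction of change and time since withdrawal (mean 2.7 against about 6.2 months; 11 of 21 against 1 of 21 control ward-months in the first two months at a six-ward site). It also coincides with the loss of ward 2W and the expected case-mix change at Western. The planned covariates do not separate these from the service model.

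The exposure counts rest on monthly steps, no gap between studies and independent random orders. The size and direction of any bias cannot be known from the documents: under the assumed ramps, rejection with equal models ranges from the nominal 5% to about a quarter.

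A reader might infer that the main results are compromised. They are not: the comparisons with no service within each study, the non-inferiority analysis and the stopping rules do not use this interaction.

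**What to change.** 1. Restrict the grand meta-analysis to the 11 wards that take part in both studies.
2. Replace the sentence that equates the interaction with a difference between models. State that it is an indirect, non-randomised, exploratory comparison confounded with study period and time since withdrawal, and that a significant interaction is not by itself taken as a difference between models.
3. As a sensitivity analysis only, add terms for time since change, both after withdrawal and after restoration.

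**Cost.** No new data. Ward 2W leaves this one analysis, and the permitted conclusion is weaker. The sensitivity analysis loses precision. In a joint least-squares fit of both studies at one six-ward site, with ward and step effects separate by study, an indicator for the first two months after withdrawal raises the interaction SE by about 26% (22–31% over the 720 orders). Adding the matching indicator after restoration brings the increase to about 52%. Any cut at two months is also arbitrary. For these reasons the terms should not be required in the main model.

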#### **Deviation from registered trial protocol**

There have been two changes to the registered trial protocol. The first change was the withdrawal from both study 1 and study 2 of what was planned to be a third study site. Originally, a third site with five participating wards was planned to be involved and the appropriate ethics approval was gained. The ethics committee at this site retracted this approval due to subsequent opposition from senior medical staff. Project investigators met with these senior medical staff to discuss their concerns; however, agreement could not be reached regarding the issues raised to enable the trial to continue at this site.

The second change was that the broader health network, within which the Western Health (Footscray) site operates, decided to transfer some services from that site to another site within their network. This has resulted in only 5 wards being available to participate in study 2 at this site. This is likely to result in some changes to case-mix at the Western Health (Footscray) site during study 2. These changes are planned to take effect in early 2015 when the intervention phase of study 2 is in progress,

thus it was decided to make the changes to the study wards involved from the commencement of phase 2.

## Discussion

Disinvestment from health services is becoming a growing priority for health care service providers due to increasing health care expenditure, budget cuts, an increasing burden of chronic disease and ageing in developed nations, and the ongoing introduction of new health technologies that render older technologies obsolete [39–41]. Paradigms for undertaking disinvestment are emerging but current processes rely upon the availability of evidence of effectiveness and cost-effectiveness [39,42,43]. This study uses a novel research design to demonstrate how health services can generate evidence regarding effectiveness, cost-effectiveness and safety during the disinvestment process [21]. The withdrawal of an intended study site due to opposition from senior medical staff despite prior ethics approval has demonstrated a clear barrier to conducting disinvestment research.

## Trial status

Recruitment ongoing, anticipated completion June 2015.

## Additional file

**Additional file 1: SPIRIT 2013 Checklist: recommended items to address in a clinical trial protocol and related documents\*.**

## Abbreviations

ARD-RG: Australian Refined Diagnosis-Related Group; EQ-5D-5 L: European Quality of Life, 5 dimensions; QALY: quality-adjusted life year; TIDieR: Template for Intervention Description and Replication.

## Competing interests

The authors declare that they have no competing interests.

## Acknowledgements

Funding for this trial has been received from a partnership grant from the National Health and Medical Research Council (NHMRC) Australia (ID 1060696) and from the Department of Health, Victoria. TH is supported by a Career Development Fellowship from the NHMRC (ID 1069758).

## Access to trial data

TPH will have access to the final, de-identified trial dataset.

**Submit your next manuscript to BioMed Central and take full advantage of:**

- Convenient online submission
- Thorough peer review
- No space constraints or color figure charges
- Immediate publication on acceptance
- Inclusion in PubMed, CAS, Scopus and Google Scholar
- Research which is freely available for redistribution

Submit your manuscript at  
[www.biomedcentral.com/submit](http://www.biomedcentral.com/submit)

[figure not shown]

Supplement: S1 Text — Study protocol for 2 randomised controlled trials examining the effectiveness and safety of current weekend allied health services and a new stakeholder-driven model of weekend allied health services for acute medical/surgical patients versus no weekend allied health services. (PDF) [file pmed.1002412.s004.pdf]
